### Variables

The following variables will be identified in cases and controls: age; gender; reason for admission; inter and intra-wards transfers; admission from home or other acute or long-term care institutions; previous hospitalisation; surgical procedures; Intensive Care Unit (ICU) stay (previous 12 months); residency in long-term care facility; transfer form another hospital; nursing and/or medical domiciliary assistance; urinary catheter; central venous catheter (CVC, at hospital admission); underlying conditions (Infectious Disease-specific Chronic Disease Score, CDS-ID); room sharing with a ESBL or MRSA patient; previous MRSA or ESBL carrier; consciousness at admission; antibiotic therapy (previous 30 days).

Antibiotic therapy will be reported as for daily dosage, frequency of dosage(s), route of administration, type of antibiotic(s), reason for starting and stopping, duration of therapy. At every clinical follow-up the following variables will be also detected: presence of urinary catheters; CVC; surgery; room sharing with a ESBL or MRSA positive patient; MRSA or ESBL-producing gram-negative infections (including type of infection, therapy, and outcome); albumin, creatinine and blood urea nitrogen levels.

### Microbiological methods

#### Methicillin resistance detection in Staphylococcus aureus

Dedicated personnel will be trained in performing nasal samples. Both nostrils will be sampled. Specimens obtained with a dry swab (Copan, Italy) will be incubated overnight in 2 ml of Mueller-Hinton broth supplemented with colistin 32 μg/mL and 2.5% NaCl (CS) at 35°C in room air. Then 10 μl of broth sample will be plated onto chromogenic medium (MRSAid, bioMérieux, Marcy l'Étoile, France) [11] and will be incubated overnight (18-24 h) at 35°C. The growth of > 1 colonies will indicate methicillin-resistance. The isolation of *S. aureus *will be confirmed through the use of a classical DNase assay or automated phenotypic methods (VITEK2, bioMérieux, Marcy l'Étoile, France, or PhoenixTM, Becton Dickinson, Burlington, NC) [12]. Oxacillin-resistant colonies will be isolated and stored in Trypticase Soy Broth (Becton Dickinson, Burlington, NC) and glycerol 20% at -80°C in freezer vials.

#### Extended spectrum beta-lactamases detection in Enterobacteriaceae

Rectal specimens will be obtained with a dry swab (Copan, Italy) and will be inoculated onto plates of ESBL chromogenic medium (Brillaince ESBL, Oxoid, Basingstoke, UK). After the direct plating, 1 ml of trypticase soy broth (TSB) with 0.5% NaCl will be added to the transport tube and the selective broth will be incubated overnight at 37°C in air. The selective medium will be plated on the ESBL chromogenic medium following the same procedure as for direct plating. Colonies will be identified according to manufacturers' recommendations and subcultured for confirmatory testing. The ESBL phenotype of identified colonies of *Klebsiella *species, *Escherichia coli *and *Proteus *species will be detected by confirmatory double disk diffusion test (DDT). Ceftazidime (30 μg), cefotaxime (30 μg), or cefepime (30 μg) discs will be placed on Mueller-Hinton agar plates, 20 mm apart (centre to centre) from a clavulanate disc (clavulanic acid 10 μg). The test will be considered as positive when a decreased susceptibility to cefotaxime is combined with a clear-cut enhancement of the inhibition zone of cefotaxime in front of the clavulanate-containing disk, often resulting in a characteristic shape-zone referred to as 'champagne-cork' or 'keyhole' [12,13]. Plates will be incubated overnight (18-20 h) at 35°C. ESBL-producing bacteria will be stored in microbanks (Pro-Lab Diagnostic, Canada) at -80°C.

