## Abstract

**Background:**

The risk of acquisition of antibiotic resistant-bacteria during or shortly after antibiotic therapy is still unclear and it is often confounded by scarce data on antibiotic usage.

Primary objective of the study is to compare rates of acquisition of methicillin-resistant *Staphylococcus aureus *and extended spectrum beta-lactamase-producing *Enterobacteriaceae *in hospitalised patients, after starting antibiotic therapy.

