## Testing the hypothesis

All adult patients (> 18 years) starting intravenous and/or oral antibiotic treatments during hospitalisation will be included in the study. Written informed consent will be obtained by every patient before study inclusion. Exclusion criteria will be pregnancy and recent nose surgery. Patients starting antibiotic therapy *per os *and/or intravenously will be sampled at antibiotic start (t_0_, within one hour) and at the following intervals: day 3 (t_1_), 7 (t_2_), 15 (t_3_), 30 (t_4_) (Figure 1). Patients colonised with MRSA and/or extended-spectrum β-lactamase (ESBL)-producing gram-negative bacteria before starting antibiotic therapy (t_0 _sample) will be excluded from follow-up cultures and analysis. Patients will be followed during the hospitalisation and afterwards for a total of 30-day from the inclusion in the study. Screening will be performed in outpatient clinics after patients' discharge from the hospital, if possible.

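### The ESBL confirmatory rule reads only the cefotaxime disc and covers three groups of bacteria, which matches neither the discs named nor the Enterobacteriaceae endpoint, so ESBL carriage and acquisition may be misclassified

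*Protocol article*

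**What the plan says.** All references are to the protocol article. The section on ESBL detection plates rectal swabs on a chromogenic ESBL medium, directly and after overnight broth. It continues: "Colonies will be identified according to manufacturers' recommendations and subcultured for confirmatory testing". That sentence sets no limit on genus. The next sentence describes confirmation for Klebsiella species, E. coli and Proteus species, whose phenotype in the last of these and the other two "species will be detected by confirmatory double disk diffusion test (DDT"). No other genus is mentioned.

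For the discs it says: "Ceftazidime (30 μg), cefotaxime (30 μg), or cefepime (30 μg) discs will be placed on Mueller-Hinton agar plates", each set at a fixed distance from a clavulanate disc. The result is then "positive when a decreased susceptibility to cefotaxime is combined with a clear-cut enhancement of the inhibition zone of cefotaxime" facing clavulanate. No reading is given for ceftazidime or cefepime. The section ends by providing for frozen storage of ESBL-producing bacteria only.

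The target organism is worded in more than one way:
- The abstract and the Statistical analysis section speak of ESBL-producing Enterobacteriaceae. The abstract begins "Primary objective of the study is to compare rates of acquisition of methicillin-resistant" S. aureus and these Enterobacteriaceae.
- The t0 exclusion in Testing the hypothesis concerns patients colonised with ESBL-"producing gram-negative bacteria before starting antibiotic therapy".
- The Sample size section uses the gram-negative wording for 443 cases, then the Enterobacteriaceae wording for the centre targets.

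**The concern.** The positivity rule and the sentence before it do not fit together. Three cephalosporin discs are named, but only one can change the result. The word 'or' also allows, on a literal reading, a plate that lacks the one disc the rule needs. The organisms given a confirmatory route are narrower than the family named in the endpoint.

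The same test does several jobs. It decides who is negative at t0 and so enters the longitudinal analysis. It decides who counts as an ESBL acquisition in the primary outcome, which is also to be reported by antibiotic class and single drug. It decides who is a case and who may serve as a control. A missed acquirer is analysed as a non-acquirer and may be drawn as a control in Case control study 2. A carrier missed at t0 stays in the cohort, and could later be counted as newly colonised if a further isolate is read differently. With three hospitals in three countries, an ambiguous rule may also be applied differently by centre.

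**Working it through.** **Step 1. Discs against rule.** Apply the text literally to each pattern of clavulanate enhancement.

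| Enhancement seen on | Result under the stated rule |
|---|---|
| Cefotaxime, with decreased susceptibility to it (with or without the others) | Positive |
| Ceftazidime only | Negative |
| Cefepime only | Negative |
| Plate without a cefotaxime disc | Rule cannot be applied |

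Two of the three named discs therefore have no stated effect on classification.

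**Step 2. Organisms against endpoint.** Klebsiella, E. coli and Proteus have a confirmatory route. For any other Enterobacteriaceae recovered from the chromogenic medium the article states none. Such an isolate is either not counted, which lowers the count, or counted on chromogenic growth without confirmation, which could raise it. The text does not settle which.

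**Step 3. The planned ESBL count.** Inputs from the Sample size section: 8565 patients, 3% MRSA, 5% ESBL, 257 and 443 cases.
- MRSA: 8565 × 0.03 = 256.95, which agrees with 257.
- ESBL: 8565 × 0.05 = 428.25, which does not agree with 443; 443/8565 = 5.17%.
- Centre targets: 95 + 201 + 147 = 443.

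The 443 is thus the sum of the centre targets and not 5% of 8565. That is a separate matter; 443 is used below because it is the stated target.

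**Step 4. Illustration of missed cases.** The document gives no enzyme or species mix and no test sensitivity. The missed share m is therefore an assumption, taken as 5% to 20%. Missed = 443 × m.
- m = 0.05: 443 × 0.05 = 22 missed, 421 detected.
- m = 0.20: 443 × 0.20 = 89 missed, 354 detected.

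**Step 5. Misclassified controls in Case control study 2.** Share of non-cases who are missed acquirers = missed/(8565 − detected), ignoring baseline exclusions and MRSA cases.
- 22/(8565 − 421) = 22/8144 = 0.3%. With 4 × 421 = 1684 controls, about 5.
- 89/(8565 − 354) = 89/8211 = 1.1%. With 4 × 354 = 1416 controls, about 15.

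**Step 6. Effect on a rate ratio between two drugs.** With perfect specificity, and ignoring small changes in antibiotic-days, observed ratio = true ratio × (sensitivity for drug A / sensitivity for drug B).
- Equal sensitivity, for example 0.80/0.80: a true ratio of 1.0 stays 1.0.
- 0.90/0.80: 1.0 becomes 1.13.
- 0.90/0.70: 1.0 becomes 1.29.

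The unequal values are hypothetical. Nothing in the article links test sensitivity to the drug received.

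**The case against.** The strongest reply is that this is a journal article. Bench rules for each disc and genus commonly sit in a laboratory manual or full protocol, and the cefotaxime sentence may merely describe the typical appearance of a positive test. A laboratory would ordinarily place all three discs, so the literal reading of 'or' is strained. This has some force. But the article does not leave the rule out: it states one, and that rule does not fit the discs listed just before it. This is a mismatch in stated text, not missing detail.

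Other parts of the objection stand and limit the point:
- **Uneven error by drug.** A reader might infer that rates by drug are distorted because particular antibiotics select the strains that the rule misses. The document does not support this. One test wording applies to all patients, and no enzyme or species data are given.
- **Certain loss of cases.** A reader might infer that acquisitions in other genera will be missed. They may instead be counted unconfirmed.
- **Different targets.** A reader might infer that the gram-negative wording sets a wider case target. In the Sample size section both terms label the same 443 cases, so this is loose wording.
- **Controls.** Even under the assumed range, misclassified controls are about 1% or fewer.
- **Retesting.** Because only ESBL-producing bacteria are stored, isolates recorded negative cannot be assumed to exist for a second reading.

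**Conclusion.** The point holds as a defect in the stated case definition. The rule uses one of the three discs named, and confirmation covers three groups while the endpoint is a whole family. ESBL carriage at t0 and ESBL acquisition may be misclassified as a result.

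The size is unknown. The 22 to 89 of 443 rests wholly on the assumed 5% to 20% and on error that runs only towards missed cases. If under-detection is equal across drugs, the harm falls on absolute rates per 1,000 antibiotic-days and on the number of cases, while comparisons between drugs are about unchanged. Differential error remains a possible risk that the document neither shows nor excludes. The change should be made: the mismatch is plain, it touches the primary outcome, and it is cheap to remove.

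**What to change.** - Require ceftazidime, cefotaxime and cefepime discs together ('and', not 'or'), and call the test positive when clavulanate enhancement is seen with any of them.
- Either apply confirmation to every Enterobacteriaceae species recovered, or restrict the named endpoint to ESBL-producing E. coli, Klebsiella and Proteus. State how any other isolate is classified.
- Use one organism term for the t0 exclusion, the endpoint and the case targets.
- From now on, keep isolates that grow on the chromogenic medium but fail confirmation, so that they can be retested. Do not rely on retesting past negatives.
- Record the date of the change at each centre, and note the isolates read under the old rule or handle them in a sensitivity analysis.

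The cost is a laboratory-manual amendment while recruitment is under way, up to two more discs per suspect isolate, some further freezer storage, and a change of reading rule partway through the study that the analysis must acknowledge. Wider confirmation adds work for each additional species tested.

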### Statistical analysis

The assessable population for each target organism will include all treated patients from whom baseline screening and at least one follow-up screening will be available. The incidence of colonisation will be defined by the number of new cases of colonisation for 1,000 days of antibiotic therapy. Only patients with a negative baseline (t_0_) will be included in the longitudinal analysis. The length of exposure to antibiotic therapy for patients newly colonised by ARB will be defined by the number of days between the inclusion in the study and the date of the first positive sample. The length of exposure to antibiotic therapy for patients not colonised will be defined by the number of days between the inclusion in the study and the date of antibiotic discontinuation. The colonisation pressure will be calculated for each center and defined as the average point of prevalence for antibiotic-resistant bacteria for all days until acquisition or discharge. Time-to-event analysis (in days) between the inclusion in the study and the acquisition of colonisation will be done using Kaplan-Meier curves and Cox proportional hazard regression modeling in which the number of days until acquisition will be the dependent variable. Two nested case-control studies will be performed:

#### Case control study 1

To define the impact of antibiotics on new acquisition of MRSA and ESBL-producing *Enterobacteriaceae*, a matched case-control study will be done (ratio 1:4). The control group will be selected among patients not receiving antibiotics, admitted in the same ward on the day of the corresponding case, with negative cultures at hospital admission. Matching criteria will include: age (± 5 years), sex, and total length of hospitalisation.

#### Case control study 2

To define individual level of risk related to specific antibiotics, patients acquiring MRSA and ESBL-producing *Enterobacteriaceae *will be compared with patients not acquiring ARB after starting antibiotic therapy (ratio 1:4). Previously known risk factors or clinically relevant significant variables from the univariate analysis will be considered for inclusion in multivariate logistic regression analysis. The Hosmer and Lemeshow goodness-of-fit test will be used to assess model fit.

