**Methods/Design:**

The study, running in three European hospitals, is a multicenter, prospective, longitudinal, observational cohort study funded from the European Community's Seventh Framework Programme [FP7/2007-2013] within the project 'Impact of Specific Antibiotic Therapies on the prevalence of hUman host ResistaNt bacteria' (acronym SATURN). Nasal and rectal screening for methicillin-resistant *Staphylococcus aureus *and extended spectrum beta-lactamase-producing *Enterobacteriaceae *will be obtained at hospital admission, discharge, at antibiotic start (t_0_, within one hour) and at the following intervals: day 3 (t_1_), 7 (t_2_), 15 (t_3_), and 30 (t_4_). Two nested case-control studies will be performed. The objective of the first study will be to define individual level of risk related to specific antibiotics. Patients acquiring methicillin-resistant *Staphylococcus aureus *and extended spectrum beta-lactamase-producing *Enterobacteriaceae *(cases) will be compared with patients not acquiring antibiotic-resistant strains after starting antibiotic therapy (controls; ratio 1:4). To define the impact of antibiotics on new acquisition of target antibiotic-resistant bacteria, a second nested case-control study will be done (ratio 1:4). Control group will be selected among patients not receiving antibiotics, admitted in the same ward on the day of the corresponding case, with negative cultures at admission. Epidemiological, clinical and microbiological data will be prospective collected.

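### At-risk status rests on the t0 swab alone, so a patient positive at admission and negative at t0 can count as a new acquisition; the t0 exclusion also conflicts with the per-organism population

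*Protocol article*

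**What the plan says.** The Methods/Design part of the abstract states that nasal and rectal screening "will be obtained at hospital admission, discharge, at antibiotic start" and at later intervals. Two results may therefore exist before treatment: the admission swab and the t0 swab.

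Only t0 decides who is at risk. The Statistical analysis section says "Only patients with a negative baseline (t_0_) will be included in the longitudinal analysis", and Testing the hypothesis likewise ties exclusion to the t0 sample. The listed exclusion criteria do not mention a positive admission swab. Earlier carriage is recorded as a variable ("previous MRSA or ESBL carrier", Variables) but excludes nobody.

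The admission result is used in one place: controls in case-control study 1 are untreated patients "with negative cultures at hospital admission". No such condition is stated for the cases.

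On organisms, Testing the hypothesis says that "Patients colonised with MRSA and/or extended-spectrum β-lactamase (ESBL)-producing gram-negative bacteria before starting antibiotic therapy" "will be excluded from follow-up cultures and analysis". The Statistical analysis section is worded by organism: "The assessable population for each target organism will include all treated patients", provided that a baseline and at least one follow-up screen are available.

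**The concern.** The primary outcome counts new acquisitions per 1,000 antibiotic-days. A patient already positive on a study swab at admission, whose t0 swab is negative and whose day 3 swab is positive, meets the plan's definition of newly colonised although the study's own data show earlier carriage. The same patient can serve as a study 1 case, while a patient with the same admission result cannot be a control, so eligibility differs between the two sides of that comparison.

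The second part concerns who is removed. A patient with ESBL but no MRSA at t0 is still at risk of acquiring MRSA. Read literally, the and/or rule ends that patient's cultures and analysis for both organisms. The per-organism population does not bring the patient back, because it requires a follow-up screen that the exclusion rule stops.

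**Working it through.** **The plan's own figure.** Sample size gives 8,565 patients, 257 MRSA acquisitions and a 3% rate: 8,565 × 0.03 = 256.95, and 257 / 0.03 = 8,567. This reproduces, and it shows no deduction for patients removed at t0. I use 8,565 as the base below.

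**Part 1: admission-positive, t0-negative, later positive.** The document gives no carriage prevalence p and no single-swab sensitivity s, so both are assumed. I also assume that carriage persists, that swab errors are independent, that every patient has both swabs, and that k follow-up swabs are taken. For one organism:

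false acquisitions = 8,565 × p × s × (1 − s) × [1 − (1 − s)^k]

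| p | s | k | Calculation | Result |
|---|---|---|---|---|
| 2% | 0.9 | 1 | 171.3 × 0.09 × 0.90 | 13.9 |
| 5% | 0.8 | 2 | 428.25 × 0.16 × 0.96 | 65.8 |
| 10% | 0.8 | 2 | 856.5 × 0.16 × 0.96 | 131.6 |

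For scale, 14 is 5% of the 257 planned MRSA events and 3% of the 443 planned ESBL events; 132 is 51% and 30%. The last row is not a ceiling: 10% carriage, 70% sensitivity and two follow-up swabs give 856.5 × 0.21 × 0.91 = 163.7.

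Using the admission swab removes these patients but not carriers missed on both swabs. In the third row those number 8,565 × 0.10 × 0.2² × 0.96 = 32.9, so all carriers missed at t0 and found later number 131.6 + 32.9 = 164.5 (164.4 unrounded).

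**Part 2: and/or exclusion against organism-specific exclusion.** Carriage at t0 is again assumed, and the two organisms are taken as independent.

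| t0 carriage, MRSA / ESBL | At risk, and/or rule | At risk for MRSA, organism-specific | At risk for ESBL, organism-specific | Expected MRSA events at 3% |
|---|---|---|---|---|
| 2% / 5% | 8,565 × 0.98 × 0.95 = 7,974 | 8,394 | 8,137 | 239 against 252 |
| 5% / 10% | 8,565 × 0.95 × 0.90 = 7,323 | 8,137 | about 7,708 | 220 against 244 |

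The fraction of the MRSA at-risk group that is lost equals the ESBL carriage, and the reverse holds for ESBL.

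**The case against.** **t0 is the natural start of risk, and the controls have no t0.** The question is acquisition after starting antibiotics, and study 1 controls never start them. Requiring a negative admission culture of controls is therefore not an error in itself. This stands. The point is narrower: no admission condition is stated for the cases.

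**Some admission-positive, t0-negative patients may truly have cleared.** This also stands; the calculation treats them all as missed carriers. A later positive would still not be a first acquisition.

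**The admission swab may be less available than it looks.** It appears for the cohort only in the abstract; the main-text schedule for treated patients runs from t0 to t4. Completeness and the admission-to-t0 interval are not given, and where antibiotics start at admission the two swabs may not be separate tests. Hence the fix says where one was taken, and the gain may be smaller than calculated.

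**Both culture methods include broth enrichment**, which any assumed sensitivity should reflect. The low end of the range, 14 patients, is therefore as legitimate as the high end.

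**A reader might infer that missed carriers inflate drug effects**, because the Background says antibiotics select pre-existing resistant bacteria. The document does not support a direction. The whole cohort is treated, so bias between drugs depends on how missed carriage and its later detection differ by drug. Non-differential error would tend to dilute contrasts. Recorded previous carriage is also available to the multivariable model.

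**A reader might also set all carriers missed at t0 against the planned 3% and 5%.** With 10% carriage, 80% sensitivity and two follow-up swabs, that group is 0.02 × 0.96 / 0.92 = 2.1% of t0-negative patients. The group at issue is the admission-positive subset, 131.6 / 8,565 = 1.5% of those enrolled. Nor are 3% and 5% shown to be rates free of missed carriers: one comes from an earlier study, the other from retrospective case-control studies.

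**The organism conflict may only be wording in a condensed article.** For the analysis rule that is possible. But the text also stops follow-up cultures, and swabs not taken cannot be recovered at analysis.

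**Conclusion.** The point holds as one of definition. As written, a treated patient with a positive admission swab, a negative t0 swab and a later positive swab is a new acquisition in the primary outcome and an eligible study 1 case, although an admission-positive patient is not an eligible control.

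Its size is conditional on the assumptions above: about 14 patients in the mildest scenario shown and about 132 in the heaviest tabulated one, out of 8,565. Correlated swab errors, or antibiotics started at admission, would lower these numbers. No direction of bias in comparisons between drugs is shown.

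The exclusion of carriers of either organism contradicts the per-organism population, and the two passages must be reconciled. At the assumed carriage levels the cost is 13 to 24 expected MRSA events (252 − 239; 244 − 220), and each rate is confined to patients free of the other organism.

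**What to change.** 1. For each organism, define at risk as negative for that organism at t0 and on the admission swab where one was taken.
2. Apply the same admission-negative rule to the cases of case-control study 1.
3. Add a sensitivity analysis that excludes patients recorded as previous carriers.
4. Make the t0 analysis exclusion organism-specific, and align Testing the hypothesis with the Statistical analysis section.
5. State whether carriers of one organism stay in follow-up for the other. If they do, state that this adds their scheduled swabs and applies only to patients whose cultures have not already stopped.

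Items 1 to 3 use data the study already plans to collect and lose a few patients. Items 4 and 5 together are more than a change of wording. On the assumed carriage levels, carriers of exactly one organism number 8,565 × (0.02 × 0.95 + 0.05 × 0.98) = 582 to 8,565 × (0.05 × 0.90 + 0.10 × 0.95) = 1,199, each with up to four screens from t1 to t4. Recruitment is under way, so follow-up already ended cannot be restored.

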### Outcomes

The primary outcome will be the rate of acquisition of target antibiotic bacteria by 1,000 antibiotic-days in hospitalised patients. The rate will be also defined according to antibiotic class and single drug. Patients will be stratified by class of risk (e.g., cirrhosis, diabetes, malignancies) and rate of acquisition will be defined. The secondary outcome will be the rate of nosocomial infections by 1,000 days of hospitalisation in newly colonised patients after undergoing antibiotic therapy.

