## Implications of the hypothesis

SATURN project is a European multicentre study that aims to provide an in-depth knowledge of ARB acquisition through the analysis of antibiotic classes, duration of treatment and dosage in the nosocomial setting by a multidisciplinary approach. The SATURN project website http://www.saturn-project.eu provides the information and details concerning the different WPs and the entire project.

Several outcomes will be obtained at the end of the study (December 2014, expected): the rate of acquisition of target ARB by 1,000 antibiotic-days according to different classes of antibiotics, duration of therapy, and antibiotic combinations (monotherapy versus combinations); risk factors associated with new colonisation by target ARB; and risks for nosocomial infections due to target ARB after a cycle of antibiotic therapy adjusted by length of hospitalisation and ward colonisation pressure.

The WP4 study is currently recruiting patients in all clinical centers. The accomplishment of the study will be pursued thanks to the great strive of all clinicians, nurses and microbiology staff in every study step. An advertising campaign (posters, stickers and pictures) was performed in the selected wards in order to thrill and sensitise the recruited staff.

The results of the study should lead to the design of specific infection control measures for preventing spread of ARB in hospitalised non-ICU patients undergoing antibiotic therapy. A potential benefit for selective screening in high-risk patients during antibiotic therapy or shorter duration of antibiotics in such patients might be hypothesised. Readily available colonisation information could impact empiric therapy for nosocomial infections or, for example, the potential need of mupirocin prophylaxis for patients colonised by MRSA during hospitalisation. Assessment of the usefulness of the recommendations derived from the results of the SATURN study should be of valuable help for those in charge of infection control, for hospital administrators, and for those managing budgets of large healthcare organisations.

We do expect that SATURN project results will have a direct impact on clinical practice, improving the appropriateness of antibiotic prescribing policy, the prevention of antibiotic-resistant infections and the heightener of patients' quality care.

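### The primary rate divides acquisitions from up to 30 days by antibiotic-days that, for non-acquirers, end when the drug stops, so rates depend on course length

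*Protocol article*

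**What the plan says.** Under Outcomes, the protocol article states: "The primary outcome will be the rate of acquisition of target antibiotic bacteria by 1,000 antibiotic-days in hospitalised patients". It adds: "The rate will be also defined according to antibiotic class and single drug". Under Implications of the hypothesis it promises "the rate of acquisition of target ARB by 1,000 antibiotic-days according to different classes of antibiotics, duration of therapy, and antibiotic combinations".

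Statistical analysis gives the definition: "The incidence of colonisation will be defined by the number of new cases of colonisation for 1,000 days of antibiotic therapy". It then fixes the length of exposure to antibiotic therapy by two rules, chosen by outcome:

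- newly colonised patients: "the number of days between the inclusion in the study and the date of the first positive sample";
- patients not colonised: "the number of days between the inclusion in the study and the date of antibiotic discontinuation".

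Testing the hypothesis schedules swabs on days 3, 7, 15 and 30 and follows each patient for 30 days from inclusion, whatever the length of the course. Swabs after discharge are taken in outpatient clinics where feasible. Nowhere does the article restrict the counted acquisitions to those found during therapy.

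**The concern.** A patient who stops the drug on day 5 and is first positive on day 30 adds one event and 30 antibiotic-days, 25 of them off the drug. A patient with the same course and the same swabs, all negative, adds 5 days; the other 25 observed days at risk are dropped. Since most patients do not acquire the organism, the denominator is close to the total course length, while the numerator can gather events over the whole 30 days.

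The mismatch can also run the other way. One follow-up swab is enough to be assessable, so a non-acquirer last swabbed on day 3 but treated to day 14 counts as 14 event-free days, 11 of them unobserved.

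This is the primary outcome, and the article plans to compare it by class, by single drug and by duration of therapy. If classes differ in usual course length, part of the difference between their rates comes from the definition and not from the drugs. A drug given in short courses tends to look worse per antibiotic-day. That matters because the article hopes to inform prescribing and raises shorter courses as a possible benefit.

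**Working it through.** The article states no expected rate per 1,000 antibiotic-days for this study, so there is no planned rate to reproduce. The one input taken from it is consistent with its own figures: Sample size gives 3% MRSA acquisition after starting therapy, and 257/8565 = 3.0%.

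**Inputs from the article:** 3% acquisition; swabs on days 3, 7, 15 and 30; the two exposure rules.

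**Assumptions, not in the article:** the 3% is read as a 30-day risk under a constant hazard; every swab is taken; one course length L per drug; the hazard after stopping is a fraction r of the ordinary on-therapy hazard.

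**Formulas**

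- Ordinary daily hazard: h = −ln(1 − 0.03)/30 = 0.001015, or 1.0 per 1,000 days.
- Still negative at day t: S(t) = exp[−h_on·min(t, L) − r·h·max(0, t − L)], where h_on is h, or 2h for the doubled drug.
- First positive at swab k: p_k = S(t_(k−1)) − S(t_k).
- The plan's rate: 1000·Σp_k / [Σp_k·t_k + S(30)·L].

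**Worked case, r = 1, ordinary hazard**

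- p = 0.00304, 0.00404, 0.00803 and 0.01489; sum 0.0300.
- Acquirers' days per patient enrolled: 0.00304×3 + 0.00404×7 + 0.00803×15 + 0.01489×30 = 0.605.
- L = 5: non-acquirers add 0.97×5 = 4.85 days. Rate = 1000×0.0300/5.455 = 5.5.
- L = 14: non-acquirers add 0.97×14 = 13.58 days. Rate = 1000×0.0300/14.185 = 2.1.
- By the same formula, L = 3, 7 and 21 give 8.5, 4.1 and 1.4. The hazard is 1.0 per 1,000 days in all of them.

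**Doubled on-therapy hazard, L = 14, r = 1:** events 0.0437; days 0.738 + 0.9563×14 = 14.127; rate 3.1.

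**Range over risk after stopping (per 1,000 antibiotic-days)**

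| Post-stop hazard, fraction of h | 5-day drug, hazard h | 14-day drug, hazard h | 14-day drug, on-therapy hazard 2h |
|---|---|---|---|
| 1 | 5.5 | 2.1 | 3.1 |
| 0.5 | 3.4 | 1.6 | 2.6 |
| 0.25 | 2.2 | 1.3 | 2.3 |
| 0 | 1.0 | 1.0 | 2.0 |

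h is held fixed, so the 30-day risk is 3% only in the first row at hazard h; at r = 0.5 it is 1.8% (5 days) and 2.2% (14 days). In the last column the post-stop hazard is not doubled. If it is doubled too, the column reads 4.1, 3.1, 2.6 and 2.0, and its order against the 5-day drug is the same in every row.

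**What drives it (r = 1)**

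- Counting everyone to the first positive swab or day 30 gives 1000×0.0300/(0.605 + 0.97×30) = 1.0 at every course length.
- Using actual antibiotic-days in everyone but still counting all 30-day events gives 6.0 at 5 days and 2.2 at 14 days, so the artefact remains.
- The main cause is thus the non-acquirers' clock stopping while events continue to count. Acquirers' extra days only lower the rate a little (6.0 to 5.5, and 2.2 to 2.1).
- With a constant hazard, about 90% of first positives come on swabs after a 5-day course has ended: (0.0300 − 0.00304)/0.0300. For 7- to 14-day courses it is about 76%: (0.0300 − 0.00304 − 0.00404)/0.0300.

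**The case against.** **Counting to day 30 is inferred.** The article does not say in terms that positives found after the drug stops enter the antibiotic-day rate. The primary outcome concerns hospitalised patients, and swabs after discharge are not guaranteed. This is fair. But new cases are counted without any limit to time on therapy, the acquirers' clock runs to the swab whether or not the drug has stopped, and follow-up is 30 days. Counting them is the natural reading.

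**The large figures need substantial, lasting risk after stopping and complete swabbing.** This stands.

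- If the on-therapy hazard persists for 7 days after stopping and then ends, the ordinary 5- and 14-day drugs score 2.4 and 1.5, and the doubled drug 3.0: distortion without reversal.
- If swabbing ended at the first scheduled swab on or after stopping, courses of 3, 5, 7, 14 and 21 days would score 1.0, 1.4, 1.0, 1.1 and 1.4, with no short-course gradient.
- Missing late swabs do not reliably help, though. With swabs only to day 15 and r = 1, the ordinary 5- and 14-day drugs score 3.0 and 1.1; with swabs only to day 7, they score 1.4 and 0.5, so the long course is then understated.

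**Stronger readings that the article does not support.** A reader might infer that every ranking of drugs in the study is distorted. Case-control study 2, which addresses the risk of specific antibiotics by logistic regression, does not use this denominator. The Kaplan-Meier and Cox analyses are defined as time from inclusion to acquisition with no censoring rule stated, so they are not shown to inherit the two clocks. A reader might also infer that any analysis of duration must be biased, but duration of therapy is listed separately under Variables and can be analysed without this exposure length. Nor does every class comparison of the rate shift: where course lengths are equal, only the level is wrong.

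**Conclusion.** The defect is real and lies in the definition of the primary rate: as written, numerator and denominator cover different windows, and the denominator rule depends on the outcome. It reaches the breakdowns of that rate by class, drug and duration wherever course lengths differ.

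Its size runs from nothing to a reversed order. With equal hazards, the 5-day to 14-day ratio of rates is 5.5/2.1 = 2.6 if risk is unchanged after stopping and 1 if risk ends at the stop. A true doubling on therapy is ranked in the wrong order when post-stop risk equals or is half the on-therapy risk, and is nearly invisible (2.3 against 2.2) when it is a quarter. These figures rest on a constant hazard, complete swabbing and assumed course lengths. The article does not give the post-stop risk, but its Background treats acquisition soon after therapy as part of the question, so zero cannot be presumed. That the ranking will reverse is not established; that the rate can mislead is.

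**What to change.** In Statistical analysis, replace the two exposure rules with one clock for all patients: from t0 to the first positive swab, or to the last negative swab in those who stay negative. Using the recorded drug dates, split that time into on-antibiotic days, including one prespecified carry-over window, and off-antibiotic days. For each rate, count only the events that fall in the state whose days form the denominator. Make the on-antibiotic rate the one broken down by class, drug and duration, and report the off-antibiotic rate separately. State how an event between two swabs is dated, since this decides its state.

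The cost is wording and some programming; swab dates and therapy duration are already to be collected. The on-antibiotic rate will rest on fewer events, dating between swabs leaves some ambiguity, and reported rates will usually be lower. Switching to actual antibiotic-days in everyone while still counting all 30-day events would not be enough.
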